### Strategies to improve adherence to interventions {11c}

All health care providers on the ICUs will be trained to prescribe only the study fluids in all included patients. In addition, patients and their family members will receive comprehensive information with the consent procedure including the importance of completing the follow-up. Furthermore, they receive contact details of the respective study team in case questions or concerns should arise.

Except for the choice of fluid given, all other treatment required will be provided within the standard of care for all patients. Protocol deviations will be recorded in the database.

### Relevant concomitant care permitted or prohibited during the trial {11d}

All concomitant treatments are permitted during the study, with the exception of the administration of maintenance or resuscitation fluids other than the blinded study fluid (e.g. normal saline or Ringer’s lactate solution, colloids, dextrose).

### Provisions for post-trial care {30}

As this study is a comparison of two already established fluid protocols, no harm is anticipated.

### Outcomes {12}

#### Primary endpoint

The primary endpoint is the occurrence of clinically relevant vasospasm requiring immediate intervention as mentioned above during ICU/IMC stay. Clinically relevant vasospasm will be defined as any vasospasm requiring medical intervention (conservative or endovascular). The outcome will be analysed as a dichotomous variable.

#### Secondary endpoints

Secondary endpoints entail ICU and in-hospital mortality and 90-day mortality (aggregated as proportions of patients), treatment modalities for vasospasms (conservative vs. endovascular treatment—proportion of patients, number of days), need for decompressive hemicraniectomy (proportion of patients), evidence of brain oedema requiring intervention (proportion of patients), occurrence of hyper- or hyponatraemia (proportion of patients and number of days with hyper- or hyponatraemia), length of ICU and hospital stay (days), and neurological outcome at day 90 (ordinal scale) (see also Table 1).

**Table 1 Tab1:** Outcomes

Primary endpoint	Occurrence of clinically relevant vasospasm requiring immediate intervention during ICU/IMC stay
Secondary endpoints	
Mortality	ICU- and in-hospital mortality 90-day mortality
Length of stay	Length of ICU/IMC stay Length of hospital stay
Treatment modalities for vasospasms	Vasospasms requiring endovascular treatment Vasospasms managed conservatively
Brain oedema	Requiring any of the following: - Deep sedation - Ventricular drainage - Hyperventilation - Osmotherapy - Decompressive craniectomy
Electrolytes	Occurrence of hyponatraemia Occurrence of hypernatraemia
Neurological outcome at 90 days	Assessed by: - Modified Rankin Scale - Glasgow Outcome Scale Extended - Mini Montreal Cognitive Assessment

*ICU *Intensive Care Unit, *IMC *Intermediate Care Unit

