## Introduction

### Background and rationale {6a}

Non-traumatic subarachnoid haemorrhage (SAH) is a devastating disease with a high mortality of up to 50% [1]. More than 50% of the survivors develop cognitive dysfunctions in the long term and never return to their previous status [1]. Most of these patients are Younger than 55, so the disease has a major socio-economic impact in addition to the individual tragedy [1, 2].

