## Statistical methods

### Statistical methods for primary and secondary outcomes {20a}

This is a parallel group study. All randomised patients receiving the study fluid will be included in the primary analysis according to a modified intention-to-treat (mITT) principle [38]. The analysis is defined as modified because patients in whom an AV-malformation is subsequently identified as the source of the haemorrhage will be excluded, since this underlying condition falls outside the intended study population; their data will contribute only to a drop-out analysis. Normal distribution of continuous variables will be tested with the Shapiro–Wilk test. Normally distributed variables are presented with mean and standard deviation. Skewed or interval and ordinal variables are presented as medians with interquartile ranges. Normally distributed interval and ordinal variables will be compared by unpaired *t*-test and skewed variables by the Wilcoxon rank sum test. Comparisons of categorical variables were performed using chi-square test or Fisher’s exact test, as appropriate [39].

Whether the use of normal saline significantly influences our primary endpoint will be assessed by a logistic regression analysis adjusted for the stratification variables (trial site) in the ITT population [40]. For the primary endpoint, deceased patients or patients who were transferred prior to reaching the primary endpoint will be counted as “no event”. A sensitivity analysis with a modified primary endpoint will be used, defined as a composite endpoint of (i) clinically relevant vasospasms during the first 14 days, (ii) ICU/IMC readmission during the 14 days (if discharged earlier) because of vasospasms, or (iii) death within 14 days.

Our secondary endpoints will be assessed by logistic (binary endpoints) as well as linear regression models (such as mRS, GOSE, and miniMOCA) adjusted for the stratification variable (trial site).

We will report absolute risk difference and relative risk ratios with 95% CIs for dichotomous secondary outcomes. For continuous secondary outcomes, we will report mean differences with 95% CIs. Missing values will be imputed with the use of the last-observation-carried-forward method for measurements made after baseline. *P* values smaller than 0.05 are considered statistically significant. Secondary outcomes will be analysed in an explorative way.

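### Length of stay is to be reported as a mean difference in days with no rule for patients who die, so an arm with more early deaths can appear to have shorter stays

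*Protocol article*

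**What the plan says.** The Secondary endpoints section names "length of ICU and hospital stay (days") without further definition. Table 1 repeats it as length of ICU/IMC stay and length of hospital stay. ICU, in-hospital and 90-day mortality are separate secondary endpoints.

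The section on statistical methods for primary and secondary outcomes {20a} contains four statements that bear on it:

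- The model: "Our secondary endpoints will be assessed by logistic (binary endpoints) as well as linear regression models", adjusted for trial site. The examples given for the linear model are the neurological scales. Length of stay is not named, but it is a secondary endpoint measured in days.
- The effect measure: "For continuous secondary outcomes, we will report mean differences with 95% CIs".
- The test, in a general paragraph on comparing variables: "skewed variables by the Wilcoxon rank sum test".
- The population, stated for the primary analysis: "All randomised patients receiving the study fluid will be included in the primary analysis", with late-found AV-malformations removed. Patients who die are not removed.

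The same section does have rules for death, but only for the primary endpoint. There, "deceased patients or patients who were transferred prior to reaching the primary endpoint will be counted as" having had no event, and a sensitivity analysis adds death within 14 days to a composite. Nothing comparable is given for length of stay.

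**The concern.** Death ends a hospital stay, as discharge does, but it is the opposite outcome. A mean of observed days treats the two alike, so a patient who dies on day 3 contributes a lower value than one who recovers and leaves on day 14. A difference between arms in early mortality then becomes a difference in length of stay that says nothing about recovery.

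This setting is exposed to the problem. The background describes "a devastating disease with a high mortality of up to 50" per cent. The rationale draws on evidence that crystalloid choice affects mortality in other critically ill groups, and mortality is itself an endpoint. The Recruitment section says that most patients remain in ICU/IMC for 14 days, so an early death would cut the observed stay well short. At stake is the direction of a published estimate: the fluid with more early deaths could be reported as shortening ICU and hospital stay.

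**Working it through.** The article states no figure for length of stay, so there is nothing of its own to reproduce. The check asks how large the distortion could be.

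**Formula.** Let survivors stay S days on average in both arms, and let those who die stay D days on average. With mortality m, an arm's mean stay is (1 − m)·S + m·D. With mortality m1 and m0 in the two arms, the difference is −(m1 − m0)·(S − D). It is zero if mortality is equal or if those who die stay as long as survivors.

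**Inputs, all assumed except the 160 per arm from the Sample size section:**

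- ICU: survivor stay log-normal, median 14 days, log-SD 0.5, so S = 14·exp(0.5²/2) = 15.86 days; D = 5 days.
- Hospital: survivor stay log-normal, median 21 days, log-SD 0.6, so S = 21·exp(0.6²/2) = 25.14 days; D = 6 days.
- Death times exponential; mortality 20% in one arm and 20%, 25% or 30% in the other.

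**Results.** The last two columns are the proportions of simulated trials with p < 0.05, using tests on raw stay including deaths, not adjusted for site.

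| Mortality | ICU difference | Hospital difference | t-test | Wilcoxon |
|---|---|---|---|---|
| 20% vs 20% | 0 | 0 | about 5% | about 5% |
| 25% vs 20% | 0.05 × 10.86 = 0.54 d shorter | 0.05 × 19.14 = 0.96 d shorter | 8–9% | about 10% |
| 30% vs 20% | 0.10 × 10.86 = 1.09 d shorter | 0.10 × 19.14 = 1.91 d shorter | 18–19% | 24–27% |

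The rank test rejects more often than the t-test because early deaths take the most favourable ranks. Switching to Wilcoxon for skewed data therefore does not help.

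**Other assumptions.** Take mean survivor stay as 14 days (ICU, SD 6) or 25 days (hospital, SD 12), deaths at a mean of 3 to 8 days (SD 3), and 136 analysable patients per arm (160 less 15%). A 5-point mortality gap then shortens ICU stay by 0.3–0.55 days and hospital stay by 0.85–1.1 days. A 10-point gap gives 0.6–1.1 and 1.7–2.2 days. The standard errors are about 0.7–0.9 and 1.55–1.75 days, so the shift is at most about 1.3 standard errors. The chance of a nominally significant shorter stay rises from 2.5% to about 6–9% (5-point gap) or 13–25% (10-point gap).

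**What a death-aware ranking shows.** Give every death the worst rank and keep survivor stays identical. At 30% against 20% mortality, the chance that a random patient from the higher-mortality arm fares worse than one from the other arm, counting ties as half, is 0.30 × 0.80 + ½ × (0.30 × 0.20) + ½ × (0.70 × 0.80) = 0.24 + 0.03 + 0.28 = 0.55. The comparison now points against the arm with more deaths, whereas the raw mean favours it.

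**The case against.** A reader might infer that the plan prescribes counting deaths as short stays. It does not. The article is silent, and observed days, survivors only, a worst value or a competing-event analysis would all be compatible with it. The full protocol and any SAP are not shown and may contain the rule. What stands against this defence is that the article already fixes the summary, a mean difference in days, and gives death rules for the primary endpoint but none here. A later document would have to revise that summary as well as fill a gap.

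A reader might also infer that the length-of-stay result will be reversed. That does not follow either. It needs an imbalance in early deaths, and the article gives no timing of death and no mortality by arm. The hypothesis concerns vasospasm, and the Discussion cites a small subgroup of SAH patients with no significant mortality difference, which it calls underpowered. Excluding patients with clear limits to therapy at admission also removes some early deaths.

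The assumed ICU stays do not match the Recruitment section closely. Under them only about 37% and 41% of patients in the two arms stay at least 14 days, whereas the article expects the vast majority to do so. The figures are therefore illustrations, not predictions.

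Finally, raw stay including deaths is a legitimate measure of resource use, the article never calls a shorter stay a benefit, the endpoint is exploratory, and mortality is reported beside it. All of this stands and lowers the priority. It does not make the mean difference interpretable as an effect on recovery.

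**Conclusion.** The point holds in limited form. The article fixes a mean difference in days for length of stay and gives no rule for deaths. If deaths enter with their observed days, an arm with more early deaths can appear to have a shorter stay, and the Wilcoxon test shares the fault. On the main assumptions the shift is roughly half a day (ICU) to one day (hospital) for a 5-point mortality gap, and 1.1 to 1.9 days for a 10-point gap. False-positive rates are 8–9% and 18–19% by t-test. These figures rest on identical survivor stays, deaths well before the usual discharge time, and assumed mortality. With equal mortality the bias disappears. Priority is low to moderate.

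**What to change.** State the rule for deaths before unblinding. Make the between-arm comparison time to discharge alive from ICU/IMC and from hospital. Deaths in the unit or in hospital either take the worst rank, in a site-stratified rank test or site-adjusted ordinal model, or are treated as a competing event in a site-adjusted analysis. Present raw length of stay descriptively, separately for survivors and non-survivors, in place of the mean difference.

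The cost is analysis wording. The comparison needs only the discharge dates and vital status that length of stay and ICU and in-hospital mortality already require. Days alive and out of hospital to day 90 would also deal with deaths, but it needs readmission and post-transfer dates that the article does not say are collected. The drawback of the proposed measure is that it mixes stay and survival, so it must be read beside mortality and no longer gives a simple difference in days.

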#### Pre-planned substudies

In pre-planned substudies, we aim to analyse the following: (1) electrolyte shifts over the course of the duration of the active study phase, (2) fluid accumulation during ICU or IMC stay, (3) neuro-cardiac interactions, and (4) blood pressure dynamics in the context of vasospasms.

### Participant timeline {13}

All eligible patients will be randomised within 24 h of diagnosis (time stamp on first computed tomography or MRI). From randomisation up to discharge from ICU/IMC or day 14 after randomisation, whichever comes first, the patient will receive the allocated study fluids only. Fluid, water, and electrolyte balance will be assessed daily. Serum osmolality and urinary sampling will be performed at hospital admission (day 1) and on days 3, 7, 10, at day 14, or at the day of ICU/IMC discharge, whichever comes first. In addition, blood gas analysis including electrolytes will be performed at a minimum of once a day as long as the patient is in ICU/IMC. In addition, an electrocardiogram and, at the lead centre (University Hospital Bern, Inselspital), bioimpedance measures will be performed on predefined study days (see Table 2 [SPIRIT figure]).

**Table 2 Tab2:**
[figure not shown]
SPIRIT figure

Neurological outcome will be assessed by the modified Rankin Scale (mRS), Glasgow Outcome Scale Extended (GOSE), and Montreal Cognitive Assessment (miniMOCA) at day 90 (see Supplementary Figures S1–S3). Mortality will be assessed at day 30 and 90.

### Sample size {14}

Sample size calculation was based upon our ICU’s registry data (PDMS). In 2017, 71/160 (44.38%) patients with SAH reached our predefined endpoint of clinically relevant vasospasm requiring immediate intervention. Studies evaluating other prophylactic measures against vasospasm, such as clazosentan, magnesium, or cilostazol, have reported relative risk reductions ranging from approximately 10% to 50% [37]. Based on these findings, we considered the expected effect of the fluid intervention to lie in the mid-range, corresponding to about a 30% relative risk reduction. With an assumed baseline event rate of 45%, this translates into an absolute risk reduction of approximately 15 percentage points. The sample size was calculated with the Power and Sample Size Calculator provided by the Statistical Institute of the Medical University of Vienna (http://statistics.msi.meduniwien.ac.at) and cross checked on http://powerandsamplesize.com. The calculation revealed that at least 160 patients per group are required to detect a reduction of 15% of clinically relevant vasospasms with an alpha-error of 0.05, a power of 80%, and a drop-out rate of 15%.

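### A 30% relative reduction of a 45% event rate is 13.5 points, not 15, and the favourable rounding takes power at 160 evaluable per group from about 79% to about 70% (two-sided alpha assumed)

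*Protocol article*

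**What the plan says.** All of this stands in the protocol article, Sample size {14}. The control rate comes from the lead unit's own registry: "In 2017, 71/160 (44.38%) patients with SAH reached our predefined endpoint". The section then cites trials of other prophylactic measures, with relative reductions of roughly 10% to 50%, and puts the expected effect of the fluid in the middle of that range, "corresponding to about a 30% relative risk reduction". The next sentence makes the conversion: "With an assumed baseline event rate of 45%, this translates into an absolute risk reduction of approximately 15 percentage points". The number of patients, at least 160 per group, is the number "required to detect a reduction of 15% of clinically relevant vasospasms", with alpha 0.05, 80% power and 15% drop-out.

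The 15% in that last sentence has to mean percentage points. The preceding sentence says so, and a relative reduction of 15% (45% to 38.25%) would need 836 evaluable per group.

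**The concern.** The only argument given for the effect size is the relative one: 30% is the middle of the cited range. The figure that sets the number of patients is the absolute one. The text says that the second follows from the first, and it does not. The sample size is therefore that of a somewhat larger effect than the one argued for.

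This bears on how a neutral result would be read. A reader who takes 30% as the expected effect and 80% as the power would think the trial better able to detect that effect than it is.

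**Working it through.** **Inputs** (Sample size {14} unless noted): baseline 45%; registry rate 71/160 = 44.38%; relative reduction 30%; absolute reduction 15 points; alpha 0.05; power 80%; 160 per group, 1:1 (320 in total, Study setting {9}). Sidedness is not stated for the calculation. Two-sided is assumed here, and one-sided is shown at step 5.

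**1. The conversion.**
- 0.30 × 45% = 13.5 points, so 45% to 31.5%.
- 15 / 45 = 33.3% relative, so 45% to 30%.
- The registry rate does not help: 0.30 × 44.38% = 13.3 points, and 15 / 44.38 = 33.8%.

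**2. The plan's own figure, 45% vs 30%.** Write d for the difference, p̄ for the mean of the two rates, A = √[2p̄(1−p̄)] and B = √[p1(1−p1) + p2(1−p2)].
- Unpooled: n = (1.960 + 0.842)² × B² / d² = 7.849 × 0.4575 / 0.0225 = 159.6, so 160.
- Pooled: n = (1.960A + 0.842B)² / d², with A = 0.6847 and B = 0.6764, gives 162.3, so 163.

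The stated 160 is thus reproduced as the number of evaluable patients per group for 15 points, before any drop-out.

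**3. The same formulas for 45% vs 31.5%.**
- Unpooled: 7.849 × 0.4633 / 0.018225 = 199.5, so 200.
- Pooled, with A = 0.6873 and B = 0.6806: 202.3, so 203.

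That is about 25% more (200 / 160 = 1.25; 203 / 163 = 1.25).

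**4. Power, pooled, two-sided:** Φ[(d√n − 1.960A) / B].

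| Evaluable per group | 15 points | 13.5 points | Difference |
|---|---|---|---|
| 160 | 79.4% | 70.2% | 9.2 |
| 136 (160 less 15%) | 72.7% | 63.1% | 9.6 |

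For example, at 160: 15 points gives (1.897 − 1.342) / 0.6764 = 0.821, Φ = 0.794; 13.5 points gives (1.708 − 1.347) / 0.6806 = 0.530, Φ = 0.702. From the registry rate, the figures at 160 are 79.7% for 15 points and 69.2% for a 30% relative reduction.

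**5. One-sided alpha of 0.05, at 160 per group.**
- 15 points: (1.897 − 1.645 × 0.6847) / 0.6764 = 1.140, Φ = 87%.
- 13.5 points: (1.708 − 1.645 × 0.6873) / 0.6806 = 0.848, Φ = 80%.

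The levels rise, but a gap of about 7 points remains.

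**The case against.** The strongest reply is that this is rounding. The section hedges both figures, the support is a loose analogy with drug trials, and 33% lies in the mid-range of 10% to 50% nearly as well as 30% does. The plan nowhere argues for exactly 31.5% in the saline group. This stands, and it is why the effect can simply be restated as one-third. It does not rescue the sentence as written. Thirty per cent is the exact midpoint of the cited range, 13.5 does not round to 15, and the rounding goes in the favourable direction. Power is sensitive here: at 160 per group it is 73% for a 31% relative reduction and 76% for 32%, and it reaches 79% only at about 33%.

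A second reply is that the power claim is attached to the 15-point reduction, not to the relative one. That is correct. A reader might infer that the stated 80% power is simply false because of the conversion. The text does not support this: for 15 points, with 160 evaluable per group and two-sided alpha, the power is 79–80%. What fails is the statement that 15 points is what a 30% reduction amounts to.

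A third reply concerns sidedness. The hypothesis in Objectives {7} is directional, and at one-sided 0.05 a 13.5-point difference has 80% power at 160 evaluable per group. The document does not state a one-sided test, and the general threshold of P below 0.05 in Statistical methods {20a} is most naturally read as two-sided. No choice of sidedness makes 30% of 45% equal 15 points.

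**Conclusion.** The conversion is wrong as written, and no other section corrects it. Its own effect, at two-sided 0.05, is a fall in power from about 79% to about 70% at 160 evaluable per group, or equivalently 200–203 rather than 160–163 evaluable per group for 80% power.

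A reader might go further. Adding 15% drop-out to 200–203 gives about 236–239 per group (200 / 0.85 and 203 / 0.85, rounded up), and it is tempting to set that against 160 and charge the whole gap to this error. That would mix two matters. The 160 matches the two-sided number before drop-out, so the drop-out allowance appears not to have been added, and that shortfall exists for 15 points as well. With 136 evaluable per group, power is about 73% for 15 points and 63% for 13.5 points, and only the difference between these two belongs here.

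The error does not touch the validity of the final estimate or its confidence interval. It is a misstatement of the planning effect and of the power that goes with it.

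**What to change.** Rewrite the conversion in one of two ways:

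- State the planning effect as 45% to 30%, that is 15 percentage points or a one-third relative reduction, and say why one-third is plausible within the cited range.
- Keep the 30% relative reduction, state it as 13.5 points (45% to 31.5%), and give the power as about 70% with 160 evaluable per group.

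In either case state whether alpha is one- or two-sided, and write "percentage points" in the sentence that gives the sample size. A two-line table with the power for both effects would make the position clear.

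The cost is two sentences and, under the second option, a less favourable figure. No enlargement of the trial is proposed, and no endpoint or analysis changes. Trial status reports 157 patients randomised and Interim analyses {21b} plans none, so the restatement can be made before any comparative result is known.

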## Methods: participants, interventions, and outcomes

### Study setting {9}

The study will be carried out in accordance with the protocol and with principles enunciated in the current version of the Declaration of Helsinki, the guidelines of Good Clinical Practice (GCP) issued by ICH [13, 14]. We plan to enrol 320 patients (1:1 randomisation) at Intensive Care Units at the University Hospital Bern, Inselspital, Bern, at the University Hospital Geneva, HUG, Geneva, and at the Canton Hospital St. Gallen.

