### Methods in analysis to handle protocol non-adherence and any statistical methods to handle missing data {20c}

A logistic regression analysis in the per protocol population adjusted for the stratification variable (trial site) is planned. Missing data is handled by the last observation carried forward method. In case the number of drop-outs exceeds the expected rate of 15%, the excess drop-outs will be replaced by recruitment of new subjects.

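### The 160 per group is the size before drop-out: with the planned 15% loss, two-sided power is about 73%, not 80%

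*Protocol article*

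**What the plan says.** Section {14}, Sample size, starts from registry data in which "71/160 (44.38%) patients with SAH reached our predefined endpoint". It rounds this to 45% and takes an absolute reduction of about 15 percentage points, so the comparison is 45% versus 30%. It then concludes that "at least 160 patients per group are required to detect a reduction of 15% of clinically relevant vasospasms with an alpha-error of 0.05", and the same sentence adds "a power of 80%, and a drop-out rate of 15" per cent. The natural reading is that 160 per group delivers 80% power after 15% of patients have dropped out.

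Section {9}, Study setting, fixes the total: "We plan to enrol 320 patients (1:1 randomisation". The Trial status section counts 157 randomised patients as 49%, which confirms that 320 is the number randomised, with no reserve on top.

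Section {20c} adds a replacement rule: "In case the number of drop-outs exceeds the expected rate of 15%, the excess drop-outs will be replaced". Drop-outs up to 15% are therefore not replaced.

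Section {14} does not say whether alpha is one- or two-sided. Section {20a} says only that P "values smaller than 0.05 are considered statistically significant" and plans 95% confidence intervals for the dichotomous secondary outcomes.

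**The concern.** All inputs to the calculation and its result are printed, and they do not agree. The inputs reproduce 160 per group only when the drop-out rate is left out.

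This is the design figure for the primary endpoint. No interim analysis is planned (section {21b}) at which the size might be revisited. If the text stands, a null result will be read as coming from a trial with 80% power for a 15-point reduction after the expected losses, which the design does not have.

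**Working it through.** **Inputs.** Control rate 45%, intervention rate 30%, alpha 0.05, power 80%, drop-out 15% (all section {14}); 1:1 allocation and 320 patients (section {9}). Two-sided alpha is an assumption. The normal quantiles are 1.960 and 0.8416.

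**Step 1: reproduce 160.** Unpooled normal formula, no drop-out:

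n = (1.960 + 0.8416)² × (0.45 × 0.55 + 0.30 × 0.70) / 0.15² = 7.849 × 0.4575 / 0.0225 = 159.6, so 160 per group.

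Pooled formula, with mean rate 0.375:

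n = [1.960 × √(2 × 0.375 × 0.625) + 0.8416 × √0.4575]² / 0.0225 = (1.342 + 0.569)² / 0.0225 = 162.3, so 163 per group.

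The arcsine formula gives 161.9 and the continuity-corrected formula 175.4. The stated 160 is thus matched exactly by the unpooled formula before drop-out.

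**Step 2: add the drop-out.** Divide by 1 − 0.15 = 0.85:

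| Formula (two-sided) | Before drop-out | After 15% drop-out |
|---|---|---|
| Unpooled | 159.6 | 187.8 |
| Arcsine | 161.9 | 190.5 |
| Pooled | 162.3 | 191.0 |
| Continuity-corrected | 175.4 | 206.4 |

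Without continuity correction this is 188 to 192 per group, depending on formula and on when one rounds up, or 376 to 384 in total. Inflating by × 1.15 instead gives 184 to 188. No two-sided version that includes the drop-out comes near 160. The unrounded registry rate (44.38% versus 29.38%) changes little: unpooled 158.5 before and 186.5 after.

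**Step 3: power with 320 randomised and 15% lost.** 320 × 0.85 / 2 = 136 per group.

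- Unpooled: 0.15 / √(0.4575 / 136) = 2.586; 2.586 − 1.960 = 0.626; power 73.4%.
- Pooled: (0.15 × √136 − 1.342) / √0.4575 = (1.749 − 1.342) / 0.676 = 0.602; power 72.7%.
- Exact enumeration of the uncorrected chi-square test: 73.3%.

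**Step 4: power at smaller losses.**

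| Loss | Evaluable per group | Power (pooled to unpooled) |
|---|---|---|
| 0% | 160 | 79.4% to 80.1% |
| 5% | 152 | 77.3% to 78.1% |
| 10% | 144 | 75.1% to 75.8% |
| 15% | 136 | 72.7% to 73.4% |

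**Step 5: detectable difference.** At 136 per group and a 45% control rate, 80% power needs a difference of 16.3 points (pooled; 45% to 28.7%) or 16.2 points (unpooled).

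**Step 6: the replacement rule.** Section {20c} acts only above 15%, so it protects a floor of 136 evaluable patients per group, not 160.

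**Step 7: the one-sided alternative.** With one-sided alpha 0.05 the unpooled and pooled sizes are 126 and 128 before drop-out and 148 to 151 after. With continuity correction the size is 141, or 166 after dividing by 0.85 (162 to 163 if multiplied by 1.15, depending on rounding). Power at 136 per group would be 82.2% (pooled) to 82.7% (unpooled).

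**The case against.** The strongest objection is sidedness. The hypothesis and primary objective are worded directionally (fewer vasospasms with saline), and alpha is given without qualification. At one-sided 0.05, 136 per group has about 82% power, and the claim of at least 80% after 15% loss would be met. This stands as a condition on the result. It is not the likelier reading: section {20a} asks whether saline influences the endpoint without giving a direction, uses 95% confidence intervals, and applies a plain 0.05 threshold. A one-sided calculation comes near 160 after drop-out only with a continuity correction and multiplication by 1.15 rather than division by 0.85, none of which the protocol states.

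Second, the actual loss from the primary analysis may be below 15%. Section {15} expects little interference with the primary outcome, and section {20a} keeps deaths and transfers in the analysis as non-events. This limits the practical effect, and 73% is the figure for the full planned loss. It does not rescue the statement, which is about 80% power at 15% drop-out; even with no loss, power is only 79% to 80%. Some loss is also built in, since section {20a} excludes patients later found to have an AV-malformation and those not given study fluid.

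Third, the calculator output is not shown, so omission of the drop-out step is inferred from the exact match at 159.6. That is fair. The mismatch between inputs and result does not depend on how it arose.

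Finally, type I error and the validity of the primary analysis are unaffected, and a null result would be judged mainly by its confidence interval. That is true, but it does not justify leaving a wrong power figure in the protocol.

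**Conclusion.** The concern holds. Under two-sided alpha 0.05, 160 per group is the size for 45% versus 30% at 80% power with no allowance for drop-out. At the planned 15% loss the trial has about 73% power, a shortfall of roughly 7 percentage points, and the difference detectable with 80% power is about 16.3 points. Keeping 80% after 15% loss would take 188 to 192 per group, that is 56 to 64 more patients in total than the 320 planned (376 − 320 and 384 − 320).

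The result rests on two assumptions: that alpha is two-sided, which the protocol does not state, and that the full 15% leaves the primary analysis. The first is the likelier reading of the analysis section; the second is the protocol's own planning figure.

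**What to change.** Rewrite the last sentence of section {14} along these lines: about 160 patients per group (unpooled formula; 163 pooled) are required before drop-out for 45% versus 30%, two-sided alpha 0.05 and 80% power; with 320 randomised and 15% drop-out, 136 per group remain, power is about 73%, and the difference detectable with 80% power is about 16.3 points.

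The sponsor should confirm the sidedness and state it. If one-sided alpha was intended, the section must say so and show the calculation.

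Remove the claim that 320 already includes 15% drop-out, or give 188 to 192 per group as the size that would. In section {20c}, make clear that the replacement rule secures 136 evaluable patients per group.

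The restatement costs only wording in the protocol and the article, and a less favourable stated power. No extra patients are needed unless the sponsor chooses to restore 80%.
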